### Data management

#### Data collection

All information should be truthfully, accurately and timely recorded in the case report form (CRF). Scale evaluators trained in rehabilitation will be responsible for assessing the simplified Fugl-Meyer scale, modified Ashworth scale and modified Barthel index, while other scales and case reports will be recorded by researchers. In the course of the experiment, special personnel will be requested to manage the relevant data, and the personal information of participants will be kept strictly confidential. All data will be identified using participant numbers, which do not directly display participant’s personal information. Data will not be shared without the explicit permission of the researchers. At the end of the trial, the research participants should submit the CRF in time and submit the test summary according to the requirements. The research center will appoint a supervisor to check the integrity and accuracy of the CRF.

#### Case report form

In the trial, the content recorded in the CRF should be consistent with the original material. The CRF must meet the following criteria:
Data must be entered with a black pen and signedIf the participant has received more than 2 weeks of intervention and evaluation, the data of the volunteer should still be recorded and countedIf an error occurs in the record and needs to be corrected, the recorder should draw a horizontal line under the original record, then sign the amendment and indicate the date of correction. Note that it must be ensured that the original record is identifiable after modification.

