### Sample size

Our study will be designed as a randomized controlled trial, and the main outcome is whether hand spasm after stroke is relieved after treatment. Current experience shows that the previous effectiveness rate of conventional acupuncture treatment is about 50%, and the expected effectiveness rate is 85%. The significance test level is 0.05, and the test power is 0.9. Sample size is calculated by using:

$$ \mathit{\mathsf{N}}={\left(\mathit{\mathsf{U}\mathsf{\alpha }}+\mathit{\mathsf{U}\mathsf{\beta }}\right)}^{\mathsf{2}}\times \mathsf{2P}\left(\mathsf{1}-\mathit{\mathsf{P}}\right)/{\left(\mathit{\mathsf{P}\mathsf{1}}-\mathit{\mathsf{P}\mathsf{0}}\right)}^{\mathsf{2}}, $$

where, *N* is the required sample size for each treatment group, and the sample size of each group is equal. When *α* is 0.05 and *β* is 0.1, the normal distribution quantile table shows that:
$$ \mathit{\mathsf{U}\mathsf{\alpha }}\left(\mathsf{0.05}\right)=\mathsf{1.65},\mathsf{and} $$
$$ \mathit{\mathsf{U}\mathsf{\beta }}\left(\mathsf{0.1}\right)=\mathsf{1.28}. $$

*P0* and *P1* represent the original curative effect and the expected curative effect, 50% and 85%, respectively. By substituting the above parameters and values into the formulas, 63 cases will be needed for each group. Accounting for a 10% expulsion rate, the final estimated sample size will be about 70 cases per group (210 in total).

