### Elimination criteria

Patients who have been mistakenly admitted or misdiagnosedNo intervention is given to the patients after admission

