### Randomization

After signing the informed consent, participants will be randomly divided into three groups: an acupuncture group, a sham acupuncture group and a control group. Randomization will be accomplished by qualified researchers using randomization software to generate random-number sequences. In the process of randomization, allocation should be kept hidden. All patients will be randomly divided into groups in a ratio of 1:1:1. The strips revealing treatment allocation will be placed in sealed opaque envelopes with sequential numbers. After obtaining informed consent, the envelopes will be opened in turn. Patients and data analysts are not clear about the randomized grouping.

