### Intervention

The interventions in the three groups are as follows:
Acupuncture group

In addition to routine rehabilitation treatment, fascial-point acupuncture will be given five times a week for 4 weeks, with 30 min each time.

Location of fascial points: the patient will be in a sitting or supine position and the physician will be placed on the affected side. First, 75% alcohol cotton ball will be used to disinfect the patients´ dorsal between the first metacarpal bone and the second metacarpal bone and the thumb of the operator. Then, the operator will apply one-way pressure with thumb on the dorsal between the first metacarpal bone and the second metacarpal bone from the distal end to the closel end. During this process, the most obvious pain point or a cord nodule can be touched can be touched, which is the fascial point as shown in Fig. 3.

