**Fig. 3 Fig3:**
[figure not shown]
Location of fascial points

Acupuncture method: routine disinfection will be carried out on the hand of the operator and the relevant fascial point of the patient. According to individual differences of patients, different specifications and models of needles will be selected (25 mm–40 mm). Physicians quickly penetrate skin through the epidermis into the subcutaneous tissues about 1–2.5 cm with the needle tip vertical using a single-handed or two-handed needle-insertion method, and then through lifting, inserting and twisting, aim to enhance the needling sensation. The physician will stop manipulating the needle when there is a sense of needle ‘stagnation, described as being like “a fish swallowing a hook.” At the same time, pain and numbness will appear in the fascia area of the patient, and conduct to the fingers, resulting in tremor and convulsion of the hand.Pressing the needle hole with a dry, cotton-wool ball after needle removal is done to prevent bleeding. In the process of the needling operation, attention should be paid to coordinating the operation of both hands so as to achieve accuracy, rapidity of treatment, and painlessness or minimal pain.
2.Sham acupuncture group

In addition to routine rehabilitation treatment, treatment using false acupuncture beside the fascial points will be given five times a week for 4 weeks, with 30 min each time.
3.Control group

Routine rehabilitation treatment will be given five times a week for 4 weeks. Conventional rehabilitation treatment mainly includes:
Good limb position: the affected upper limb maintains the position of abduction, external rotation, elbow extension, forearm supination, wrist and finger extensionBobath’s handshake exercises: the arm is raised over the head, and the mind is used to force the limbs on both sides 10 times a time for six times a dayExercise therapy: continuous stretching of spastic muscles and joint-loosening if necessary. The induced segregation movement and other manipulations are performed after relaxation of the spastic muscle, 45 min each time once a day

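### Treatment received after randomization helps decide whose data count, so randomized patients may drop out of the comparison, possibly unequally between arms and in relation to outcome

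*Protocol article*

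**What the plan says.** Four parts of the protocol article bear on whose data are counted.

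- **Elimination criteria.** Two grounds are given: mistaken admission or misdiagnosis, and the case where no "intervention is given to the patients after admission".
- **Case report form.** If "the participant has received more than 2 weeks of intervention and evaluation, the data of the volunteer should still be recorded and" counted.
- **Randomization.** "After signing the informed consent, participants will be randomly divided into three groups". Allocation is tied to consent, not to the start of treatment.
- **Sample size.** "Accounting for a 10% expulsion rate", 63 per group becomes about 70 per group, 210 in total.

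The planned course is the same length in every arm. In the Intervention section, "fascial-point acupuncture will be given five times a week for 4 weeks" in addition to routine rehabilitation. Sham needling follows the same schedule, also on top of rehabilitation. For the control arm, "Routine rehabilitation treatment will be given five times a week for 4 weeks".

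**The concern.** Both rules depend on how much treatment a patient received, and that is known only after allocation. A patient who declines all treatment, or who stops in the first half of the course, may leave the analysis although randomized.

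Randomization makes the arms comparable at allocation. Selecting later by exposure keeps them comparable only if the selection is unrelated to arm or unrelated to outcome. Stopping early can be related to both: patients may leave because the spasm is not relieved, because they find a procedure unpleasant, or because they know they are in the arm without needling. The result would then describe patients who stayed in treatment, not all those assigned to it.

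This differs from an analysis set left for a later plan to define. The protocol itself states the rules. The Case report form rule also speaks of recording as well as counting. If sites read it as permission not to record outcomes in early stoppers, no later analysis plan could recover those values.

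**Working it through.** **1. What the text fixes**

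| Patient, after randomization | Rule | Status |
|---|---|---|
| No intervention given | Elimination criteria | Eliminated (stated) |
| 2 weeks or less of intervention | Case report form | Not counted (implied) |
| More than 2 weeks | Case report form | Recorded and counted (stated) |

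At five sessions a week the threshold is 2 × 5 = 10 of 4 × 5 = 20 planned sessions. The middle row is an inference: a condition for still counting a patient's data has little purpose unless patients who fail it are treated differently.

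**2. The plan's own allowance**

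63 / (1 − 0.10) = 70 per group. The expulsion step reproduces, and it budgets for 0.10 × 70 = 7 randomized patients per group. The article does not say which rule produces these losses, or how they split by arm.

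**3. Illustration of the bias**

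Inputs: 70 randomized per arm; 7 removals (the planned 10%); a true relief rate of 50% in every arm, so 35 of 70 relieved and no real difference. The 50% is the reference rate in the Sample size section. Who is removed is an assumption.

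Observed rate = relieved patients kept / all patients kept.

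| Removals | Arm A | Arm B | False difference (A − B) |
|---|---|---|---|
| None | 35/70 = 50.0% | 35/70 = 50.0% | 0 |
| 7 non-relieved, arm A only | 35/63 = 55.6% | 50.0% | +5.6 points |
| 7 non-relieved from A, 3 from B | 55.6% | 35/67 = 52.2% | +3.3 points |
| 7 non-relieved from each | 55.6% | 55.6% | 0 |
| 7 from A, unrelated to outcome | 31.5/63 = 50.0% (on average) | 50.0% | 0 |
| 7 relieved, arm A only | 28/63 = 44.4% | 50.0% | −5.6 points |

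Arm A can be any arm. If it is the control arm, each sign reverses for needling against control.

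**4. Effect on the false-positive rate**

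This was found by exact enumeration of the two-sided Pearson chi-square test at 5%, with 70 per arm and 50% relief in both. With everyone counted, the rate is 5.2%. With 7 non-relieved patients removed from one arm only, it is 11.0%, of which 10.4% favours that arm.

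Removing exactly 7 non-relieved patients from each arm gives 7.4%, but that excess comes from fixing the count at 7. Suppose instead that each non-relieved patient in either arm is removed independently with probability 0.2, which is 10% of the arm on average. The relief probability among those kept is then 0.5 / (0.5 + 0.5 × 0.8) = 55.6% in both arms. The counts are again binomial with equal rates, and the test keeps its nominal level. The harm in this no-difference illustration therefore comes from unequal removal that is related to outcome.

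**The case against.** The case on the other side has real weight.

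- **The 2-week discard is not written down.** The sentence can be read purely as a protection for patients who stop before 4 weeks. This stands in part: exclusion from counting is an implication. A reader might go further and infer that early stoppers' data are not recorded at all. The document does not support that. The Outcome measures section has all measurements recorded, Data collection sends all information to the case report form, and Harms covers all adverse events from entry to discharge.
- **A bias in favour of needling does not follow.** A reader might infer it because only two arms add a procedure that can be refused, and because the Intervention section describes pain and numbness with fascial-point needling. But those sensations are described only for that arm, and the same section aims for little or no pain. Fear of needling is an exclusion criterion. All arms receive routine rehabilitation, so a patient who refuses needles but has rehabilitation may not meet the no-intervention rule. Control patients who know they get no needling may also leave. No discontinuation rate by arm is given. This objection stands.
- **Some removals may precede allocation.** The Recruitment section confirms eligibility from examinations after consent, and randomization also follows consent; their order is not fixed. This stands for mistaken admissions, not for early stopping.
- **Analysis sets belong in the analysis plan.** True in general, and the silence of the Statistical analysis section is no fault here. It does not answer the point, because the exposure rules are stated in the protocol.

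**Conclusion.** The concern holds in a limited form. One rule removes untreated patients explicitly, and another implies that patients with 2 weeks or less of the 4-week course are not counted. Both can act after randomization, and a 10% loss is budgeted. Randomized patients may therefore leave the comparison because of events after allocation.

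Neither the direction nor the size of any bias can be derived from the document. The 5.6 points, and the false-positive rate of 11.0% against 5.2%, are a one-sided extreme at the planned 10%: all 7 removals non-relieved, all from one arm, and true relief of 50% everywhere. If removals are balanced, or unrelated to outcome, the average false difference is about 0. The case for amending the text does not depend on which arm would gain.

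**What to change.** Amend the protocol wording as follows.

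1. **Case report form:** state that outcome data, including the end-of-course and follow-up assessments, are recorded and counted for every randomized patient in the allocated arm, whatever number of sessions was received.
2. **Elimination criteria:** delete the absence of intervention as a reason for removal from the primary analysis.
3. **Mistaken admission or misdiagnosis:** limit removal to facts that existed before randomization, judged by someone blind to arm.
4. **Two-week threshold:** keep exposure above 2 weeks only to define a secondary per-protocol set.

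The cost is a wording amendment plus some effort at the sites, which must try to complete the already scheduled assessments in patients who stop early. Some values will still be missing and will have to be handled, and the estimated effect may be somewhat smaller than in patients who stayed on treatment.

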#### Database management and quality control

The team will take effective measures to control the quality. The data in the CRF will be entered into the database uniformly. Data-entry personnel carry out manual checks at the first time of data entry, and carry out systematic checks after all data entry has been completed. After final confirmation, the database is locked and saved. Any future changes to the database must be agreed in writing by the clinical research director, statistician and data administrator.

### Data analysis

#### Statistical analysis

Statistical analysis of research data will be performed by health statisticians and major researchers using SPSS or SAS. Pearson’s *χ*2 test or Fisher’s exact test will be used to analyze classified variables and continuous variables will be evaluated using Student’s *t* test or an appropriate non-parametric method. All statistical tests will be double-sided. The statistical significance level will be set at 5%. The measured data will be described by mean ± standard deviation. Before the analysis, the normality test and homogeneity test of variance will be carried out. If the normal distribution is satisfied, a *t* test will be used. The LSD or SNK method will be used for multiple comparisons, and the rank sum test will be used for non-normality or non-uniformity of variance.

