### Outcome measures

Therapeutic evaluation will be carried out by the same team member who will be blinded to treatment allocation. The primary evaluation indicators in this study are the hand-spasm score and the duration of spasm relief. The modified Ashworth scale will be used to evaluate the spasm of the hand (mainly including the thumb and the other four fingers) before and after treatment. After the patients have been treated with acupuncture and spasticity relieved, the timing will be started to evaluate the duration of spasticity relieved (during this period, the patient should avoid mental tension, so as not to interfere with the test results).

The secondary evaluation indicators included using electromyography (EMG) to detect the activity of the affected limbs, limb function and activity of daily living evaluation. The modified Ashworth scale will be used to evaluate the degree of hand spasm on the affected side at baseline, 4 weeks after intervention and at 1, 2, 4 and 6 months of follow-up [22]. The modified Ashworth scale was divided into 0, 1, 1^+^, 2, 3 and 4 grades, and was quantified as 0, 1, 2, 3, and 4 and 5 points, respectively (Table 1). Surface EMG will be used to record the changes in surface EMG of the upper limbs on the affected side at baseline and 4 weeks after intervention [23]. The simplified Fugl-Meyer scale will be used to evaluate the upper-limb motor function on the affected side and the modified Barthel Index will be used to evaluate activities of daily living at baseline, 4 weeks after intervention and at 1, 2, 4 and 6 months of follow-up [24, 25]. All measurements will be recorded in the data center.

**Table 1 Tab1:** Modified Ashworth scale

Grade	Assessment standard	Score
0	No increase in muscle tension	0
1	Muscle tension is increased slightly. When the affected part is passively flexed and stretched, it suddenly becomes stuck at the end of joint activity and then presents minimum resistance or release	1
1^+^	Muscle tension is increased slightly. Suddenly stuck in passive flexion and extension occurs within the last 50% of the range of ROM, and then shows minimal resistance	2
2	Muscle tension is increased significantly. Muscle tension of the affected limbs in passive motion increases significantly in most ROM ranges, but still easy to move	3
3	Muscle tension is increased severely. The affected limb’s passive movement has resistance over the whole ROM, so it is difficult to move	4

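### Four scored outcomes have a baseline value, but the stated between-arm tests do not use it as a covariate and so give up precision

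*Protocol article*

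**What the plan says.** The Outcome measures section gives each scored outcome a baseline value. For spasm: "The modified Ashworth scale will be used to evaluate the degree of hand spasm on the affected side at baseline, 4 weeks after intervention", with follow-up visits at 1, 2, 4 and 6 months. Fugl-Meyer and Barthel follow the same visits. Surface EMG is recorded at baseline and 4 weeks. The hand-spasm score is one of two primary indicators; the other is duration of spasm relief.

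The Inclusion criteria admit hand grades 1+ to 3, which Table 1 scores as 2 to 4 points, so starting severity varies. The Randomization section says "All patients will be randomly divided into groups in a ratio of 1:1:1" and mentions no stratification by starting grade.

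The Statistical analysis section names chi-square or Fisher for categorical variables and, for continuous ones, Student's t "test or an appropriate non-parametric method. All statistical tests will be double-sided". It adds a rule: check normality and variance, then use a t test, otherwise a rank sum test, with LSD or SNK for multiple comparisons. No ANCOVA, regression, mixed model or baseline covariate appears in the article.

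**The concern.** Starting severity is recorded for every patient and can differ between arms by chance, but neither the allocation as described nor the named tests make use of it. Two things are at stake. One is precision: a test that leaves out a correlated baseline gives a less precise comparison than the collected data allow. The other is the reading of this one trial: if the arms differ by chance at the start, part of that difference appears in the estimate.

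The plan also leaves open which quantity is compared. The Outcome measures section speaks of spasm before and after treatment and of changes in EMG, which points towards change scores. The Statistical analysis section does not take this up. The check therefore has to cover both readings.

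**Working it through.** **Inputs from the article.** Two-sided tests ("All statistical tests will be double-sided"). Level and power for sizing: "The significance test level is 0.05, and the test power is 0.9". Evaluable patients: "63 cases will be needed for each group".

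**Assumed.** rho = 0.3, 0.45 and 0.6 for the correlation between baseline and 4-week score; equal variances at both times; a normal approximation; and an effect that gives a post-score test 80% power. The article states none of these for the scored outcomes.

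**The plan's own figure.** The article has no power figure for any scored outcome; its sizing is for the binary relief endpoint. Its formula, with P taken as the average (0.50 + 0.85)/2 = 0.675, gives (1.65 + 1.28)^2 x 2 x 0.675 x 0.325 / 0.35^2 = 30.7, so 31 per arm, not 63. That is a separate matter. The power results below do not depend on 63; only the shifts in SD units do.

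**Step 1: variance of the comparison, relative to a post-score test.**
- post score: 1
- change score: 2(1 - rho)
- ANCOVA: 1 - rho^2

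ANCOVA is below 1 for any rho other than 0. Against change scores, (1 - rho^2) / [2(1 - rho)] = (1 + rho)/2, which is below 1 for rho < 1. So ANCOVA is more precise than both for 0 < rho < 1.

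**Step 2: power.** With 1.96 + 0.8416 = 2.8016, power = Phi(2.8016 / sqrt(variance factor) - 1.96). The extra patients a post-score test would need to match ANCOVA are 1/(1 - rho^2) - 1.

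| rho | Post score | Change score | ANCOVA | Extra patients |
|---|---|---|---|---|
| 0.3 | 80% | 66% | 84% | 10% |
| 0.45 | 80% | 76% | 88% | 25% |
| 0.6 | 80% | 88% | 94% | 56% |

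Example at rho 0.45: 1 - 0.2025 = 0.7975; 2.8016/0.893 - 1.96 = 1.177; Phi = 0.88.

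**Step 3: chance baseline imbalance.** At 63 per arm the SE of the baseline difference between two arms is sqrt(2/63) = 0.178 SD, so the 95% chance range is 1.96 x 0.178 = +/-0.35 SD. A post-score comparison carries rho times the imbalance. A change-score comparison carries (1 - rho) times it, in the opposite direction. At the edge of the range:

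| rho | Shift, post score | Shift, change score | Conditional type I error, post score | Conditional type I error, change score |
|---|---|---|---|---|
| 0.3 | 0.10 SD | 0.24 SD | 8% | 16% |
| 0.45 | 0.16 SD | 0.19 SD | 11% | 14% |
| 0.6 | 0.21 SD | 0.14 SD | 16% | 11% |

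For post scores the error is the two-sided tail beyond 1.96 of a normal with mean 1.96 rho and variance 1 - rho^2. For change scores the mean is -1.96(1 - rho)/sqrt(2(1 - rho)) and the variance (1 + rho)/2. These figures hold only given an imbalance of that size. Averaged over all randomizations the error is 5%.

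**Step 4: the binary endpoint.** The sizing rates are "the previous effectiveness rate of conventional acupuncture treatment is about 50%, and the expected effectiveness rate is 85"%. At 63 per arm, two-sided 0.05: null SE = sqrt(2 x 0.675 x 0.325/63) = 0.0835; alternative SE = sqrt((0.25 + 0.1275)/63) = 0.0774; power = Phi((0.35 - 1.96 x 0.0835)/0.0774) = Phi(2.41) = 99%. There is little power left to gain here.

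**The case against.** The strongest reply is that this is a preference about efficiency. The named tests are valid, and covariates are often left to an analysis plan that is not shown. The first half stands: nothing here is invalid or contradictory. The second half stands only in part, because the section sets a decision rule that leads to a t test or a rank sum test. An analysis plan that follows it inherits the choice.

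Several stronger readings do not hold:

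- **Bias or an inflated error rate.** A reader might infer that imbalance passes in full into the result. It enters in proportion to rho (or 1 - rho, reversed), and the tests keep their nominal 5% on average. The 8% to 16% figures describe an unlucky allocation.
- **Baseline wholly ignored.** The article may intend change scores, and relief is itself judged against the starting state. Change scores do use the baseline, but less efficiently.
- **A trial short of power.** The documents do not show this. The 80% anchor and rho are assumptions, and entry limited to three grades may lower rho for spasm.
- **Adjustment always narrows the interval and settles which outcome is compared.** The treatment effect is identical for post and change scores only in linear ANCOVA. Logistic adjustment gives a conditional odds ratio, usually with a larger standard error. In a simulation with 63 per arm, 50% versus 85%, assumed entry grades of 35/40/25% and assumed baseline slopes of -0.5 and -1.0 log-odds per point, the SE of the log odds ratio rose from 0.446 to 0.460 and from 0.447 to 0.493, with power at 99% throughout.

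**Conclusion.** The concern holds as a loss of precision. For modified Ashworth, Fugl-Meyer, Barthel and EMG, the stated tests are less precise than a baseline-adjusted analysis whether post scores or changes are compared, for any rho between 0 and 1. Under the assumptions above, a post-score comparison with 80% power would reach about 84%, 88% or 94% at rho 0.3, 0.45 or 0.6. The direction is firm; the size depends on a correlation the protocol does not give.

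The conclusion does not extend to duration of spasm relief, which has no baseline value of its own, and it matters little for the relief endpoint if 50% versus 85% is true. It should be changed, but it does not threaten the trial's validity.

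**What to change.** In the Statistical analysis section, make the main between-arm comparison of each scored outcome a model with arm and the baseline value of the same score:

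- **Fugl-Meyer, Barthel, EMG:** ANCOVA, with a transformation or a rank-based or robust version if its assumptions fail. This keeps the purpose of the present non-parametric fallback.
- **Modified Ashworth points:** ANCOVA, or proportional-odds regression with baseline grade.

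Report the adjusted effect with its 95% CI and keep the unadjusted test as supportive. State which quantity that supportive test compares, post score or change. Leave duration of relief as planned. Treat adjustment of the binary relief endpoint as optional and, if used, label the result a conditional odds ratio.

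The cost is a few sentences of text and, with baseline entered as a linear term, one degree of freedom per model. No new data or patients are needed. The change should be fixed before any unblinded results are seen, including those of the mid-term analysis at 120 patients, so that nobody later chooses between adjusted and unadjusted results.

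### Unequal variance is made a trigger for the rank sum test, which is no remedy for unequal spread; a Welch t test should be named instead (minor)

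*Protocol article*

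**What the plan says.** The protocol article, under Statistical analysis, sets the default for continuous outcomes: "continuous variables will be evaluated using Student’s *t* test or an appropriate non-parametric method". It then makes the choice depend on the trial data: "Before the analysis, the normality test and homogeneity test of variance will be carried out". If the data look normal, a t test is used. Otherwise "the rank sum test will be used for non-normality or non-uniformity of variance". LSD or SNK is named for multiple comparisons. "All statistical tests will be double-sided", at the 5% level. No Welch test or other unequal-variance method appears.

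Two other sections matter here. Under Randomization, "All patients will be randomly divided into groups in a ratio of 1:1:1", and under Sample size, "63 cases will be needed for each group", raised to about 70 for losses. Under Outcome measures, the modified Ashworth grade "was quantified as 0, 1, 2, 3, and 4 and 5 points, respectively", so that primary indicator is an ordered six-level score. The simplified Fugl-Meyer scale, the modified Barthel Index and surface EMG are secondary.

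**The concern.** The rule treats non-normality and unequal variance as the same problem with the same cure. They are different problems. A rank test is a usual answer to non-normality. It is not an answer to unequal variance: its reference distribution comes from assuming that the two arms have the same distribution. If the arms share a mean or median but differ in spread, the rank sum statistic varies by a different amount than the test assumes, and the 5% level need not hold for that comparison.

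The standard tool for unequal variance in roughly normal data is the Welch t test, which the plan does not offer. The plan therefore leaves Student's t, which pools the variances, for a test that does not handle unequal spread either. At stake is the nominal error rate for the approximately continuous outcomes, and a data-driven choice of test that could be avoided.

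**Working it through.** **Plan's own figure.** The protocol states no error rate for either test, so there is none to reproduce. The arm sizes used are the stated 63 and 70, and 63 / (1 − 0.10) = 70 reproduces. Whether 63 follows from the sample-size formula is a separate matter that does not affect this point.

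**Assumptions.** Normal outcomes with equal means; arm X has n patients and SD 1, arm Y has m patients and SD k. The document gives no SDs, so k = 2 and 3 are assumed. The 70 v 50 split illustrates uneven losses and is also assumed.

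**Rank sum test.** The test takes the variance of the estimated P(X < Y) as (1/12)(1/n + 1/m). The true large-sample variance is A/n + B/m, with

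A = arcsin(1/(1+k²)) / 2π, B = arcsin(k²/(1+k²)) / 2π.

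With V = true/assumed variance, the actual two-sided rate is 2Φ(−1.96/√V). At k = 1, A = B = 1/12, V = 1 and the rate is 5.0%.

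- k = 2: A = 0.03205, B = 0.14758.
- k = 3: A = 0.01594, B = 0.17822.

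With equal arms V = 6(A + B):

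- k = 2: V = 6 × 0.17963 = 1.078; 1.96/√V = 1.888; rate 5.9%.
- k = 3: V = 6 × 0.19416 = 1.165; 1.96/√V = 1.816; rate 6.9%.

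With 70 v 50 and the larger SD in the arm of 50, the assumed variance is (1/12)(1/70 + 1/50) = 0.002857:

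- k = 2: 0.03205/70 + 0.14758/50 = 0.003409; V = 1.193; rate 7.3%.
- k = 3: 0.01594/70 + 0.17822/50 = 0.003792; V = 1.327; rate 8.9%.

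**Student's t.** V = (1/n + k²/m) / [s²(1/n + 1/m)], with s² = [(n−1) + (m−1)k²]/(n+m−2). With equal arms V = 1, so the rate stays near 5%. At 70 v 50:

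- k = 2: s² = (69 + 196)/118 = 2.246; V = 0.09429/0.07700 = 1.22; rate about 7.7%.
- k = 3: s² = (69 + 441)/118 = 4.322; V = 0.19429/0.14818 = 1.31; rate about 8.7%.

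**Simulation, 60,000 trials per row, two-sided 5%:**

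| Arms | SD ratio | Rank sum | Student t | Welch |
|---|---|---|---|---|
| 63 v 63 | 1 | 5.0% | 5.0% | 5.0% |
| 63 v 63 | 1.5 | 5.2% | 4.9% | 4.9% |
| 63 v 63 | 2 | 5.9% | 5.1% | 5.0% |
| 63 v 63 | 3 | 7.0% | 5.2% | 5.0% |
| 70 v 50, larger SD in 50 | 2 | 7.3% | 7.8% | 5.1% |
| 70 v 50, larger SD in 50 | 3 | 8.9% | 8.8% | 5.0% |
| 50 v 70, larger SD in 70 | 2 | 4.6% | 3.1% | 5.0% |

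Formula and simulation agree. The trigger would fire: with 63 per arm, Levene's test rejected in 83% of trials at ratio 1.5 and in 99.8% at ratio 2. The whole switching procedure therefore gives 5.1% and 5.9%, much the same as the rank sum test alone.

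**Three arms of 70.** Kruskal-Wallis and the F test are alike: 5.7% v 5.8% with SDs 1, 1, 2, and 7.5% v 7.5% with SDs 1, 1, 4.

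**The case against.** Most of the defence stands and limits the point.

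- If treatment has no effect at all, the distributions are identical and the rank sum test holds its level (5.0 to 5.1% in simulation). The excess arises only under a null of equal means or medians with different spreads. The protocol does not say which null the rank sum test addresses. Describing data by mean and SD is a descriptive statement and does not settle it.
- A reader might infer that the plan replaces a sound test with an unsound one. The documents do not support that. The test given up is Student's t, which is near 5% here only because the arms are planned equal; at 70 v 50 it errs about as much as the rank sum test.
- A reader might also infer severe inflation. With skewed data and equal means, large rates do appear: with 70 per arm and gamma data with coefficients of variation 0.5 v 0.75 and 0.5 v 1.0, the rank sum test rejects in 16% and 46% of trials. But clearly skewed data reach the rank sum test through the non-normality half of the rule, not the variance half, and the result depends on the assumed null. With equal-median lognormal data at a sigma ratio of 2, the rank sum test gives 5.8% and Student's t 42%. The protocol states neither these shapes nor that null.
- The same applies to the modified Ashworth score. A rank test is a conventional choice for an ordinal score. Proportional-odds regression would not remove the sensitivity to spread, because for two arms without covariates its score test is the rank sum test.

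What the defence does not answer is the variance trigger itself. No argument makes unequal variance a reason to choose a rank test, and Welch does better for roughly normal data whether or not the arms are equal.

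**Conclusion.** The point holds as a minor weakness of method. The variance trigger leads to a test that does not address unequal variance, and the plan names none that does. For roughly normal outcomes with equal means, the cost is a rejection rate of about 6 to 7% instead of 5% at SD ratios of 2 to 3 with 63 per arm. It is about 7 to 9% at 70 v 50 with the larger SD in the smaller arm. At a ratio of 1.5 with equal arms the excess is negligible, and with the larger SD in the larger arm the rank sum test is slightly conservative at a ratio of 2 (4.6%). These sizes rest on assumed SD ratios, an assumed uneven split and normal data. They do not show that error control fails in this trial, and they give no ground for objecting to a rank test on the modified Ashworth score.

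**What to change.** Remove the homogeneity-of-variance pre-test and the clause that sends unequal variances to the rank sum test. For the approximately continuous outcomes (simplified Fugl-Meyer, modified Barthel Index, surface EMG), prespecify the Welch t test, or a linear model with robust standard errors, whatever the observed variances. Pairwise comparisons among the three arms should use the same method, because LSD and SNK rest on a pooled variance.

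For the modified Ashworth score, keep a rank-based or ordinal analysis, and state that it is chosen because the score is ordinal and not because a pre-test rejected normality.

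The cost is wording. If the variances are in fact equal, the loss of power is negligible: with equal arms the Welch and Student statistics are identical, and only the degrees of freedom fall slightly below 63 + 63 − 2 = 124. Recruitment and data collection do not change.
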